### 8.3. Evaluation of efficacy by RECIST

For patients with metastatic disease deemed non-measurable by RECIST criteria, determination of tumor response including disease progression will be made by the investigator using clinical judgement and relevant radiology, according to standard practice.

Response criteria are essentially based on a set of measurable lesions identified at baseline as target lesions, and – together with other lesions that are denoted as non-target lesions – followed until disease progression.

The following paragraphs are a quick reference to the RECIST criteria (version 1.1). The complete criteria are included in the published RECIST document [34] also available at <http://www.eortc.be/RECIST>.

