### 3.4 Endpoints

The primary endpoint is:

Proportion of patients who remain free of progression at 6 months. Progression as defined by RECIST 1.1 [34] will be used.

The secondary endpoints are:

- Proportion of patients free of progression (RECIST 1.1[34]) at 6 months in the IR-profile subgroup vs the non-IR-subgroup as defined by gene expression profiling(retrospectively defined as previously described [9])
- Proportion of patients who remain free of progression at 12 months. Progression as defined by RECIST 1.1 [34] will be used.
- Progression as defined by iRECIST [17]
- Overall survival

- Percentage of patients with toxicity (according to CTCAE v4.03, Appendix A) and immune-related toxicity defined as the Adverse Events of Special Interest (AESI's) for atezolizumab (see section 6 and Investigator's Brochure for atezolizumab)
- Objective response rate (RECIST 1.1[34])

*The exploratory endpoints are listed in Section 10 Translational Research*

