- ◆ Bilirubin  $< 1.5 \times$  upper limit of the normal range (ULN), except subjects with Gilbert Syndrome; alkaline phosphatase  $< 2.5 \times$  ULN ( $< 5 \times$  ULN in case of liver metastases, and  $< 7 \times$  ULN in case of bone metastases); transaminases (ASAT/ALAT)  $< 3 \times$  ULN (and  $< 5 \times$  ULN in case of liver metastases), **LDH  $< 2 \times$ ULN**.
- ◆ Serum creatinine  $\leq 1.5$  ULN or calculated (Cockcroft-Gault) or measured creatinine clearance  $> 40$  mL/min
- ◆ Evaluable disease or measurable according to RECIST 1.1
- ◆ Subjects with brain metastases are eligible if they have been treated, are not symptomatic and there is no magnetic resonance imaging (MRI) evidence of progression for at least 28 days prior to first dose of study drug administration. There must also be no requirement for immunosuppressive doses of systemic corticosteroids ( $> 10$  mg/day prednisone equivalents) for at least 2 weeks prior to study drug administration
- ◆ No known leptomeningeal disease localization
- ◆ No history of having received other anticancer therapies within 2 weeks of start of the study drug
- ◆ No history of immunodeficiency, autoimmune disease, conditions requiring immunosuppression ( $>10$  mg/day prednisone or equivalent) or chronic infections. Subjects with vitiligo, diabetes mellitus type I, psoriasis not requiring systemic treatment or resolved childhood asthma/atopy would be an exception to this rule. Subjects that require intermittent use of bronchodilators, inhaled steroids, or local steroid injections would not be excluded from the study. Subjects with hypothyroidism stable on hormone replacement, Sjögren's syndrome or conditions not expected to recur in the absence of an external trigger will not be excluded from the study. Adrenal replacement doses  $>10$  mg/day prednisone or equivalent are permitted in the absence of active autoimmune disease
- ◆ No prior treatment with immune checkpoint blockade such as but not limited to anti-PD(L)1, anti-PD-L2, anti-CTLA-4, anti-GITR or CD137/OX40-agonist

- ◆ No live vaccine within 2 weeks prior to start of study, at any time during the study, or within 5 months following the last dose of atezolizumab. Inactivated vaccines are allowed
- ◆ No active other cancer

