## 8 Response evaluation criteria

Response to treatment will be assessed locally and centrally. Local assessment will be used for treatment decisions during the course of the study and for assessment of the primary endpoint. After completion of the accrual, all scans made for evaluation of the disease of enrolled patients will be reviewed centrally.

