### 8.3.2 Tumor response evaluation

All patients will have their BEST RESPONSE from the start of atezolizumab until the end of treatment classified as outlined below:

**Complete or partial responses may be claimed only if the criteria for each are met at a subsequent time point at least 6 weeks later (table 2).**

Complete Response (CR): disappearance of all *target* and *non-target* lesions and normalization of tumor markers. Pathological lymph nodes must have short axis measures < 10 mm (Note: continue to record the measurement even if < 10 mm and considered CR). Tumor markers must have normalized. Residual lesions (other than nodes < 10 mm) thought to be non-malignant should be further investigated (by cytology or PET scans) before CR can be accepted.

Partial Response (PR): at least a 30% decrease in the sum of measures (longest diameter for tumor lesions and short axis measure for nodes) of target lesions, taking as reference the baseline sum of diameters. Non target lesions must be non-PD.

Stable Disease (SD): Neither sufficient shrinkage to qualify for PR nor sufficient increase to qualify for PD taking as reference the smallest sum of diameters on study.

Progressive Disease (PD): at least a 20% increase in the sum of diameters of measured lesions taking as references the smallest sum of diameters recorded on study (including baseline) AND an absolute increase of  $\geq 5$  mm. Appearance of new lesions will also constitute PD (including lesions in previously unassessed areas). In exceptional circumstances, unequivocal progression of non-target disease may be accepted as evidence of disease progression, where the overall tumor burden has increased sufficiently to merit discontinuation of treatment, for example where the tumor burden appears to have increased by at least 73% in volume (which is the increase in volume when all dimensions of a single lesion increase by 20%). Modest increases in the size of one or more non-target lesions are NOT considered unequivocal progression. If the evidence of PD is equivocal (target or non-target), treatment may continue until the next assessment, but on further documentation, the earlier date must be used.

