| Any                                                                                                                                                                                                                                                                                                                                                                                                                                                                   | PD                        | Any | PD            |                                                         |
| Any                                                                                                                                                                                                                                                                                                                                                                                                                                                                   | Any                       | Yes | PD            |                                                         |
| Patients with Non target lesions ONLY                                                                                                                                                                                                                                                                                                                                                                                                                   |                           |     |               |                                                         |
| No Target                                                                                                                                                                                                                                                                                                                                                                                                                                                             | CR                        | No  | CR            | Normalization of tumor markers, all tumor nodes < 10 mm |

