| No Target                                                                                                                                                                                                                                                                                                                                                                                                                                                             | Non-CR/non-PD             | No  | Non-CR/non-PD |                                                         |
| No Target                                                                                                                                                                                                                                                                                                                                                                                                                                                             | Not all evaluated         | No  | NE            |                                                         |
| No Target                                                                                                                                                                                                                                                                                                                                                                                                                                                             | Unequivocal PD            | Any | PD            |                                                         |
| No Target                                                                                                                                                                                                                                                                                                                                                                                                                                                             | Any                       | Yes | PD            |                                                         |

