| 
Note: Patients with a global deterioration of health status requiring discontinuation of treatment without objective evidence of disease progression [or evidence of unequivocal disease progression] at that time should be reported as “symptomatic deterioration”. This is a reason for stopping therapy, but is NOT objective PD. Every effort should be made to document the objective progression even after discontinuation of treatment.
 |                           |     |               |                                                         |

Complete or partial responses may be claimed only if the criteria for each are met at a subsequent time point **at least 6 weeks later**. The best overall response can be interpreted as below:

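### Section 8.3 scores response and progression in non-measurable disease by clinical judgement and relevant radiology, which conflicts with the RECIST 1.1 endpoints and with the protocol's own rules for non-target-only patients

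*Protocol*

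**What the plan says.** Protocol Section 3.4 sets the primary endpoint: "Proportion of patients who remain free of progression at 6 months. Progression as defined by RECIST 1.1". It makes no exception for patients without measurable lesions. The same criteria are named there for the 12-month proportion, the comparison by immune-related profile and the objective response rate. Section 9.5 again ties the primary analysis to RECIST.

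Section 5 does not require a measurable lesion; the criterion is "Evaluable disease or measurable according to RECIST 1.1".

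For metastatic disease that RECIST would call non-measurable, Section 8.3 states that "determination of tumor response including disease progression will be made by the investigator using clinical judgement and relevant radiology, according to standard practice".

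Section 8.3.1 classes all non-measurable lesions as non-target lesions. Table 2 in Section 8.3.2 then has its own block of rows, "Patients with Non target lesions ONLY", in which progression is either "Unequivocal PD" or a new lesion. The text of Section 8.3.2 adds: "Modest increases in the size of one or more non-target lesions are NOT considered unequivocal progression". The note under Table 2 says of symptomatic deterioration: "This is a reason for stopping therapy, but is NOT objective PD".

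Section 8 says who decides: "Local assessment will be used for treatment decisions during the course of the study and for assessment of the primary endpoint". All scans are to be reviewed centrally once accrual is complete. That review is not assigned to the primary endpoint, and no criteria are named for it.

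**The concern.** The sentence in Section 8.3 and the non-target-only rows of Table 2 cover the same patients and set different standards. One appeals to standard practice and allows clinical grounds. The other requires unequivocal worsening or a new lesion and excludes symptomatic decline. No section says which prevails. This is a conflict between two stated rules, not detail left for a statistical analysis plan.

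The primary result is a count of patients in a single-arm trial, scored by local assessment, with decision limits that one patient can cross: 2 against 3 of 22 at the first stage, and 7 against 8 of 40 at the end. If part of the count follows one event definition and part another, the proportion compared with 10% and 25% is not clearly the RECIST proportion that Section 3.4 names. The 12-month, profile-subgroup and response-rate endpoints have the same defect.

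**Working it through.** **1. The two rules side by side, for a patient with no target lesion**

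| Finding by 6 months | Section 8.3 sentence | Section 8.3.2 and Table 2 |
|---|---|---|
| Symptomatic decline, no objective worsening on imaging | may be called progression on clinical judgement | not objective progression |
| Modest growth of non-target disease | may be called progression | not unequivocal, so not progression |
| Unequivocal non-target worsening | progression | progression |
| New lesion | no separate rule stated | progression |

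The rules diverge in the first two rows. In both, the Section 8.3 sentence permits a call of progression that Table 2 would not.

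**2. The stated design (Section 9.2)**

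Inputs: first stage 22 patients, stop at 2 or fewer; total 40, reject at 8 or more; null 10%, alternative 25%.

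With X1 ~ Bin(22, p) and X2 ~ Bin(18, p), the rejection probability is

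R(p) = Σ over x = 3 to 22 of P(X1 = x) × P(X2 ≥ 8 − x).

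- R(0.10) = 0.0398, stated as 0.04.
- R(0.25) = 0.8032, stated as 80%.
- Probability of stopping at the first stage when p = 0.10: 0.620.

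The stated figures are reproduced. A search over two-stage designs with type I error at most 0.05 and power at least 0.80 also returns this design as the minimax one.

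**3. Sensitivity to a mixed event definition**

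The protocol gives neither the share f of patients with only non-measurable disease nor the shift d that judgement makes in their progression-free rate. Both are assumptions here: f = 10% or 20%, d = 2, 5 or 10 percentage points, all in one direction.

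- Upward shift from a true 10%: p = 0.10 + f × d
- Downward shift from a true 25%: p = 0.25 − f × d

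| f | d | null p | type I error | alternative p | power |
|---|---|---|---|---|---|
| 0.10 | 0.02 | 0.102 | 0.044 | 0.248 | 0.795 |
| 0.10 | 0.05 | 0.105 | 0.051 | 0.245 | 0.783 |
| 0.10 | 0.10 | 0.110 | 0.064 | 0.240 | 0.762 |
| 0.20 | 0.02 | 0.104 | 0.048 | 0.246 | 0.787 |
| 0.20 | 0.05 | 0.110 | 0.064 | 0.240 | 0.762 |
| 0.20 | 0.10 | 0.120 | 0.095 | 0.230 | 0.715 |

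The two error columns are alternatives, one for each direction of shift. Larger inputs give larger effects: a 40% share with a 15-point shift gives p = 0.16 and type I error 0.29, or p = 0.19 and power 0.48. Those are upper bounds, not expected values.

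**4. With one definition for everyone**

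If Table 2 applies to all patients, f × d = 0 and the design figures stay at 0.040 and 0.803 with 40 patients.

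**The case against.** The strongest reply is that the passages can be read together. The Section 8.3 sentence names relevant radiology as well as clinical judgement, and it stands under a heading about evaluation by RECIST. RECIST for non-target disease is itself qualitative: Section 8.3.1 requires no measurements of such lesions, and Section 8.3.2 turns on whether overall burden has grown enough to merit stopping treatment. On that reading, clinical judgement only describes how an investigator calls unequivocal progression without a target sum. This reading is possible, but the text does not state it. The sentence refers to standard practice rather than to Table 2, and it does not carry over the exclusions of modest growth and symptomatic decline.

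Three further points stand and limit the claim.

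- Central review covers every patient's scans, so non-target-only patients can be re-read by Table 2. Only a purely clinical call escapes that check. A reader might infer that nothing in this subset can be reproduced; the protocol does not support that.
- A reader might also infer that an investigator may disregard a new lesion judged unimportant. Section 8.3 does not say so, and Section 8.3.2 calls a new lesion progression.
- The subset may be small. Section 5 requires a non-bone metastatic lesion that can be biopsied repeatedly, which limits bone-only disease. It does not require a measurable lesion, and Section 8.3.1 lists ascites, effusions and small lesions as non-measurable.

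Finally, the binomial error rates hold for whatever event is counted. What a mixed definition puts in doubt is whether 10% and 25% are the right reference rates for that event.

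**Conclusion.** The point holds as an internal contradiction in the definition of the primary event, and of response for the objective response rate. As written it is wrong and should be fixed. It is not an error in the sample size, the decision rule or the stated error rates, all of which reproduce.

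The size is uncertain. Under the assumed 10-20% share and 2-10 point one-way shift, type I error lies between 0.044 and 0.095, or power between 0.795 and 0.715. Misclassification in both directions would partly cancel. The divergences visible in the text point towards calling progression more often, which would cost power; an upward shift is an assumption that the wording does not rule out. A reader might infer a severe inflation of type I error from a large affected share and a large shift. The protocol gives no figure to support either input, so that conclusion is not available.

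**What to change.** In Section 8.3, replace the sentence on non-measurable disease with a statement that, for all RECIST 1.1 endpoints (primary, 12-month, profile subgroup and objective response rate), patients without target lesions are scored by the non-target-only rows of Table 2 in Section 8.3.2. Confine investigator judgement in that scoring to deciding whether non-target progression on imaging is unequivocal. The change must cover response as well as progression; otherwise the same conflict remains for the response rate.

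Record clinical progression without objective progression separately, with its date and reason, and report one sensitivity analysis that counts it as failure. Leave the rules for treatment decisions as they are.

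The cost is a short text change, one case report form item, and less freedom for investigators in endpoint scoring. The sample size, stopping limits and error rates do not change.

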#### 8.3.1 Measurability of tumor lesions at baseline

##### Definitions

- **Measurable disease** - the presence of at least one measurable lesion. If the measurable disease is restricted to a solitary lesion, its neoplastic nature should be confirmed by cytology/histology.
- **Measurable lesions** - *tumor lesions* that can be accurately measured in at least one dimension (longest diameter to be recorded) as  $\geq 20$  mm with chest x-ray, and as  $\geq 10$  mm with CT scan or clinical examination [using calipers]. Bone lesions are considered measurable only if assessed by CT scan and have an identifiable soft tissue component that meets these requirements (soft tissue component  $\geq 10$  mm by CT scan). *Malignant lymph nodes* must be  $\geq 15$  mm in the short axis to be considered measurable; only the short axis will be measured and followed. All tumor measurements must be recorded in millimeters (or decimal fractions of centimeters) by use of a ruler or calipers. Tumor lesions situated in a previously irradiated area, or in an area subjected to other loco-regional therapy, are usually not considered measurable unless there has been demonstrated progression in the lesion.
- **Non-measurable lesions** - All other lesions (or sites of disease), including small lesions are considered non-measurable disease. Bone lesions without a measurable soft tissue component, leptomeningeal disease, ascites, pleural/pericardial effusions, lymphangitis cutis/pulmonis, inflammatory breast disease, lymphangitic involvement of lung or skin and abdominal masses followed by clinical examination are all non-measurable. Nodes that have a short axis  $<10$  mm at baseline are considered non-pathological and should not be recorded or followed.
- **Target Lesions.** When more than one measurable tumor lesion or malignant lymph node is present at baseline all lesions up to *a maximum of 5 lesions total* (and a maximum of *2 lesions per organ*) representative of all involved organs should be identified as target lesions and will be recorded and measured at baseline. Target lesions should be selected on the basis of their size (lesions with the longest diameter), be representative of all involved organs, but in addition should be those that lend themselves to *reproducible repeated measurements*. Note that pathological nodes must meet the criterion of a short axis of  $\geq 15$  mm by CT scan and only the *short* axis of these nodes will contribute to the baseline sum. At baseline, the sum of the target lesions (longest diameter of tumor lesions plus short axis of lymph nodes: overall maximum of 5 is to be calculated and recorded.

- **Non-target Lesions.** All non-measurable lesions (or sites of disease) including pathological nodes (those with short axis  $\geq 10$  mm but  $< 15$  mm), plus any measurable lesions over and above those listed as target lesions are considered *non-target lesions*. Measurements are not required but these lesions should be noted at baseline and should be followed as “present” or “absent”.
- All baseline evaluations should be performed as closely as possible to the beginning of treatment and never more than 4 weeks before the beginning of the treatment.

